## **Intervention**

### ***(a) Intervention group***

#### **Brief intervention via telephone (within 3 days after visiting the ED)**

The participants will receive a brief intervention using the Ask, Warn, Advise, Refer and Do-it-again (AWARD) model, which was originally developed for primary-care tobacco cessation. This intervention includes the following steps: (1) **Ask** about and assess health-risk behaviours; (2) **Warn** about the high morbidity and mortality risks associated with health-risk behaviours; (3) **Advise** on adopting healthy lifestyles to improve the participant's health; (4) **Refer** to hotline services, such as those for smoking cessation and alcohol treatment or the nearest district health centre to follow up their health status; and (5) **Do it again** if participants have not adopted a healthy lifestyle at follow-ups. For the advice step, the RA will ask about the participants' priority in engaging in a desired health-related lifestyle based on their responses in the behavioural risk factor questionnaire. The participants will also be asked to choose a goal that they consider most attainable, such as quitting or reducing smoking, consuming more vegetables or less fatty foods or sugary drinks, performing more exercise, or reducing alcohol consumption. Although the participants will be encouraged to adopt aspects of a healthy lifestyle sequentially, they will have the option to adopt them simultaneously if they feel confident in doing so. Each participant will receive a brief (approximately 5 minutes) individual intervention providing health advice on their selected lifestyle goal. The entire intervention will last approximately 10 minutes and may be extended if necessary.

At the end of the telephone call, the participant will be informed that the RA will assist them in achieving their health-related goals throughout the study by sending messages via WhatsApp/WeChat.

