#### Subjects

Chinese adults who attend one of the five EDs in various clusters in Hong Kong because of physical discomfort and if they meet the following criteria will be invited to participate. The inclusion criteria will be as follows: (1) being aged  $\geq 18$  years, (2) being triaged as semi-urgent (level 4) or non-urgent (level 5) and discharged home on the same day after receiving medical attention, (3) having at least one health risk behaviour (tobacco use, harmful alcohol consumption, unhealthy diet, and physical inactivity), and (4) owning a smartphone and having an ability to use instant messaging applications (e.g. WhatsApp or WeChat). The Exclusion criteria will be as follows: (1) having a poor cognitive state or mental illness and (2) being diagnosed with NCDs and undergoing regular follow-ups in outpatient clinics, and (3) participating in another related study.

The specific criteria for each health risk behaviour are listed in Appendix 1. People who do not have a smartphone or use WhatsApp/WeChat (unlikely in Hong Kong) will be provided brief advice and a Practical Resource Hub for Healthy Life leaflet on healthy lifestyles but will be excluded from the study.

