### **Sample size**

We used G\*Power to estimate the sample size based on the results of our pilot study conducted at an ED and a previous study using a brief smoking cessation intervention based on self-determination theory. The results of the pilot study showed an approximately 12% between-group difference in successfully adopting at least one healthy lifestyle at 6 months (the primary outcome of this proposed project). However, we opted for a more conservative effect size for our sample size calculation. Based on our previous large-scale RCT on a brief smoking cessation intervention based on self-determination theory, we expect a between-group difference of at least 5% ( $\geq 10\%$  in the intervention group vs.  $\leq 5\%$  in the control group) in the primary outcome at 6 months. To detect a significant between-group difference with a power of 80% at a significance level of 5% (two-tailed) in the proportion of participants modifying their health risk behaviours and/or adopting healthy lifestyles, 435 participants will be needed per group. To account for a potential attrition rate of 30% at the 6-month follow-up, we will recruit a total of 1,242 participants.

Based on the number of EDs visits (1.8 million) in Hong Kong between 2021 and 2022, we are confident that we will be able to recruit the required number of participants within 18 months.

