#### **Outcome measures:**

The **primary outcome** will be the number of healthy lifestyles adopted at 6 months. The criteria of successful adopting a healthy lifestyle are presented in Appendix 1.

**The secondary outcomes** will be the number of healthy lifestyles adopted at 12 months and improvement in health-related quality of life at 6 and 12 months.

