| Physical inactivity  | (1) Performed less than 150 minutes of moderate-intensity aerobic physical activity throughout the week, or (2) performed less than 75 minutes of vigorous-intensity aerobic physical activity throughout the week | Performed at least 150 minutes of moderate-intensity aerobic physical activity throughout the week, or performed at least 75 minutes of vigorous-intensity aerobic physical activity throughout the week |

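### The physical-activity success rule in Appendix 1 gives no credit for mixed exercise: 140 moderate plus 70 vigorous minutes a week fails, while 150 moderate minutes alone succeeds

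*Protocol*

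**What the plan says.** Under Outcome measures, the primary outcome "will be the number of healthy lifestyles adopted at 6 months", and the definition of success is fixed by cross-reference: "The criteria of successful adopting a healthy lifestyle are presented in Appendix 1".

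In the physical-inactivity row of Appendix 1, the success column reads "Performed at least 150 minutes of moderate-intensity aerobic physical activity throughout the week, or performed at least 75 minutes of vigorous-intensity aerobic physical activity". The risk column has two limbs: "1) Performed less than 150 minutes of moderate-intensity aerobic physical activity throughout the week, or" and "2) performed less than 75 minutes of vigorous-intensity aerobic physical activity throughout the week". Neither column has a clause for a combination of intensities, and no weighting or summing rule appears elsewhere in the protocol.

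The row is used twice. Under Subjects, a person qualifies by "having at least one health risk behaviour (tobacco use, harmful alcohol consumption, unhealthy diet, and physical inactivity", so inactivity alone is enough for entry. Under Intervention, exercise is one of the goals a participant may choose: "consuming more vegetables or less fatty foods or sugary drinks, performing more exercise, or reducing alcohol consumption".

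**The concern.** Accepting either 150 moderate or 75 vigorous minutes as success implies that a vigorous minute is worth about two moderate minutes, and certainly no less than one. The scoring then drops that equivalence for anyone who does some of each. A participant can do clearly more exercise than another and receive the worse score.

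Three things are at stake:

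- Some participants who reach the protocol's own level of activity are recorded as failures on a primary-outcome component.
- Some people who already reach it by a mix are enrolled as inactive. They cannot register success unless one intensity crosses its own cut-off.
- Because the protocol itself fixes the rule, this is not a detail it leaves open for the SAP.

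**Working it through.** **The plan's own figure.** The Sample size section states "we expect a between-group difference of at least 5" per cent (10% vs 5%), with 80% power and two-sided 5% significance. The standard two-proportion formula without continuity correction gives 435 per group (power at 435: 80.1%). Allowing for 30% attrition, 870 / 0.70 = 1,242.9. The stated 435 and 1,242 reproduce, and this point does not dispute them.

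**The rules as written.** Let M and V be weekly moderate and vigorous minutes.

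- Success: M >= 150 or V >= 75.
- At risk: M < 150 or V < 75.
- Combined total, using the ratio implied by the cut-offs (150 / 75 = 2): T = M + 2V.

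| M, V | At risk as written | Success as written | T | T >= 150 |
|---|---|---|---|---|
| 140, 70 | yes | no | 280 | yes |
| 149, 74 | yes | no | 297 | yes |
| 100, 30 | yes | no | 160 | yes |
| 150, 0 | yes | yes | 150 | yes |
| 0, 75 | yes | yes | 150 | yes |
| 150, 75 | no | yes | 300 | yes |

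The 140 + 70 participant is at 280 / 150 = 1.87 times the target and fails. The weight of 2 is not essential: the unweighted sum, 140 + 70 = 210, also exceeds 150.

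Rows four and five show a second defect. Because the risk column joins its limbs with 'or', 150 + 0 is both at risk and already a success. Changing that 'or' to 'and' would make the columns complements, but 140 + 70 would still be enrolled and still fail. The two defects are distinct.

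**Size, under assumptions only.** The protocol gives no distribution of minutes. The illustration assumes:

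- 85% do some moderate activity, median 60 or 90 min/week;
- 10% to 50% do some vigorous activity, median 30 or 45 min/week;
- the two are independent and log-normal, with SD 0.8 on the log scale;
- moderate minutes are rounded to 10 and vigorous minutes to 5.

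The between-arm columns add a second arm with both medians raised by 20%, also an assumption.

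| Doing vigorous activity | Missed, % of those with T >= 150 | Missed, points of all people | Between-arm difference, rule as written | Between-arm difference, combined total |
|---|---|---|---|---|
| 10% | 7.6-12.5 | 1.8-2.1 | 5.2-7.2 | 5.2-7.1 |
| 20% | 13.3-20.8 | 3.6-4.2 | 5.6-7.6 | 5.9-7.6 |
| 30% | 17.6-26.4 | 5.4-6.4 | 6.1-7.9 | 6.6-7.9 |
| 50% | 23.8-34.2 | 9.0-10.6 | 6.7-8.8 | 7.8-8.6 |

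Compared scenario by scenario, the combined-total difference minus the as-written difference runs from about -0.7 to +1.2 points. Both extremes occur when 50% do vigorous activity: 8.1 - 8.8 = -0.7 with medians 90 and 45, and 7.9 - 6.7 = +1.2 with medians 60 and 30.

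**The case against.** **The rule is identical in both arms.** This stands, and it limits the point most. A reader might set the 2 to 11 points of people misclassified against the planned 5-point difference. That compares a level present in both arms with a difference between arms, and most of the level cancels. A reader might also infer that the rule attenuates the treatment effect. The documents give no reason to expect more mixed exercise in one arm, since controls are also advised to adopt a healthy lifestyle. In some simulated scenarios the rule as written shows the larger difference.

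**Activity is one component of four.** This also stands. The Sample size section describes the outcome as adopting at least one healthy lifestyle. On that reading, a missed mixed exerciser changes nothing if another behaviour succeeded.

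**The simulated inputs are invented.** Correct. In the scenarios 13% to 34% meet the rule as written, against planned success of at most 5% in controls, so they are not calibrated to this trial. They show scale and direction only.

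**The protocol never states a 2:1 exchange, and two sufficient thresholds do not assert a linear trade-off.** True as to the exact weight, which is implied rather than stated. But 140 + 70 exceeds 150 even unweighted, so the misordering does not depend on it.

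**The questionnaire may hold only threshold answers.** It is not reproduced, and two yes/no items would be enough to apply Appendix 1 as written. This stands as a condition on the fix.

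**Conclusion.** The point holds as a scoring fault in a rule the protocol fixes. Read literally, Appendix 1 ranks a more active participant below a less active one, contrary to its own cut-offs, and misclassifies one of four components of the primary outcome. That conclusion follows from the text and needs no simulation.

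The frequency cannot be estimated from the protocol; the shares above rest wholly on assumed distributions. The effect on the between-arm difference is probably small and could go either way (about -0.7 to +1.2 points in the illustration). The documents do not support a claim of bias towards one arm, loss of a set part of the planned 5-point difference, or an error in the sample size. A correction is worthwhile because the fault is plain and, if minute totals are recorded, cheap to mend, and because the same row has the more serious 'or' defect, which the same edit repairs.

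**What to change.** In Appendix 1, score activity on one total, T = weekly moderate minutes + 2 x weekly vigorous minutes, and state that the weight of 2 is taken from the 150 and 75 cut-offs. Define success as T >= 150 and physical inactivity as T < 150. Use the same formula at baseline, 3, 6 and 12 months in both arms. The two columns then become exact complements, so 150 + 0 is no longer both at risk and a success.

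**Condition.** The questionnaire must record both minute totals. If it already does, the cost is one row of Appendix 1 and the scoring code; if not, the instrument needs changing. For participants already enrolled without the totals, keep the present Appendix 1 rule at baseline and report the combined score where it is available.

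**Downsides.** A few mixed exercisers would no longer qualify on inactivity alone. Nor would people who meet only one of the two cut-offs and now qualify through the 'or'; the protocol does not show how many there are. For a given set of participants, activity success can only rise under the new score, probably slightly, and it would do so in both arms.
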